## Abstract

**Background:**

Emergency department (ED) providers are important collaborators in preventing falls for older adults because they are often the first health care providers to see a patient after a fall and because at-home falls are often preceded by previous ED visits. Previous work has shown that ED referrals to falls interventions can reduce the risk of an at-home fall by 38%. Screening patients at risk for a fall can be time-consuming and difficult to implement in the ED setting. Machine learning (ML) and clinical decision support (CDS) offer the potential of automating the screening process. However, it remains unclear whether automation of screening and referrals can reduce the risk of future falls among older patients.

**Objective:**

The goal of this paper is to describe a research protocol for evaluating the effectiveness of an automated screening and referral intervention. These findings will inform ongoing discussions about the use of ML and artificial intelligence to augment medical decision-making.

**Methods:**

To assess the effectiveness of our program for patients receiving the falls risk intervention, our primary analysis will be to obtain referral completion rates at 3 different EDs. We will use a quasi-experimental design known as a sharp regression discontinuity with regard to intent-to-treat, since the intervention is administered to patients whose risk score falls above a threshold. A conditional logistic regression model will be built to describe 6-month fall risk at each site as a function of the intervention, patient demographics, and risk score. The odds ratio of a return visit for a fall and the 95% CI will be estimated by comparing those identified as high risk by the ML-based CDS (ML-CDS) and those who were not but had a similar risk profile.

**Results:**

The ML-CDS tool under study has been implemented at 2 of the 3 EDs in our study. As of April 2023, a total of 1326 patient encounters have been flagged for providers, and 339 unique patients have been referred to the mobility and falls clinic. To date, 15% (45/339) of patients have scheduled an appointment with the clinic.

**Conclusions:**

This study seeks to quantify the impact of an ML-CDS intervention on patient behavior and outcomes. Our end-to-end data set allows for a more meaningful analysis of patient outcomes than other studies focused on interim outcomes, and our multisite implementation plan will demonstrate applicability to a broad population and the possibility to adapt the intervention to other EDs and achieve similar results. Our statistical methodology, regression discontinuity design, allows for causal inference from observational data and a staggered implementation strategy allows for the identification of secular trends that could affect causal associations and allow mitigation as necessary.

**Trial Registration:**

ClinicalTrials.gov NCT05810064; https://www.clinicaltrials.gov/study/NCT05810064

**International Registered Report Identifier (IRRID):**

DERR1-10.2196/48128

## Introduction

Falls are highly prevalent among older adults in the United States [1,2] and are a common reason for emergency department (ED) visits [2-4]. They often precipitate a decline in the patient’s overall health and ability to perform activities of daily living, such as dressing, bathing, and toileting [3,5]. ED providers are important collaborators in preventing at-home falls because they are often the first providers to see a patient after a fall (secondary prevention) [1] and because outpatient falls are often preceded by previous ED visits (primary prevention) [6]. This phenomenon is especially true for patients being discharged from the ED [3].

Patients presenting to the ED are at higher risk of falls than the general population and are more likely to face barriers that limit their access to screening and interventions available in other health care settings [7-12]. While previous work has shown that ED referrals to falls prevention interventions can reduce the risk of an at-home fall by 38% [13], ED-based interventions to identify and refer high-risk older adults for falls prevention services have not been widely implemented [14]. Major barriers to fall risk screening in the ED include the additional time and resources necessary to perform in-person screening, but the integration of machine learning (ML) and clinical decision support (CDS) offers the possibility of automating the screening process, thereby making it feasible to incorporate in routine ED practice at scale without adding to provider cognitive burden [15-19]. However, it remains unclear whether the automation of such screening and referral systems can reduce the risk of future falls among older patients. The goal of this paper to is describe a research protocol for a study evaluating the effectiveness of an automated screening and referral intervention, both in terms of leading to evaluations at the Mobility and Falls Clinic and preventing future falls.

More generally, this study will provide data on the effectiveness of a model of an automated intervention to identify and refer patients during an ED visit. This model of care is extensible to many other conditions and situations in which ED patients would benefit from screening and primary or secondary prevention services.

## Methods

### Setting and Patient Population

This study takes place at 3 EDs, described in Table 1, within a health system in the Midwestern United States. All 3 EDs share an instance of the electronic health record (EHR) developed by Epic, though system configuration (eg, nursing flow sheets and order sets) is not identical at the 3 sites.

**Table 1 table1:** Intervention settings.

ED^a^ site	Type	Intervention implementation date	Approximate annual volume of patients, n	Staffing
ED 1	Academic, level 1 trauma center	February 22, 2022	60,000 (25% geriatric)	Attending group 1, advanced practice providers, residents
ED 2	Community	September 27, 2022	22,000 (28% geriatric)	Attending group 1, advanced practice providers
ED 3	Community	Planned September 2023	65,000 (20% geriatric)	Attending group 2, advanced practice providers

^a^ED: emergency department.

The patient population for our study is individuals aged 65 years or older who present to participating EDs between February 22, 2022, and spring 2026, were discharged, and who had (at the time of ED visit) a primary care provider practicing within the health system in which this study is based. Because the ML-based CDS (ML-CDS) will be implemented in a rolling fashion at different EDs within the system, the start date for data will vary at different study sites. Dates were chosen to have at least two years’ worth of index ED data for each site and an additional 6 months of follow-up ED visits to identify subsequent falls.

### Intervention

These patients will be evaluated by our ML algorithm, and patients at high risk for an at-home fall within the next 6 months were flagged by our CDS when a provider documented a disposition of discharge from the ED [20,21]. The intervention, as well as training and validation of the algorithm, are limited to this in-system patient population for 2 reasons: first, these patients have a more complete patient history in the EHR for the algorithm to draw on, and second, this restriction mitigates the possibility that access to care or insurance coverage network would be a barrier to patients being seen in the falls clinic.

The study intervention applies automation to harness existing data resources and information systems both to estimate risk at the patient level and to facilitate referral among high-risk patients. This risk estimate drives a CDS tool that presents a referral recommendation to the physician within the ED workflow. This selective application of automation is aligned with human factors principles [21-24] and allows busy clinicians to improve patient care without interruption to existing workflows.

To support efforts by ED providers to prevent falls among older adults, our team has developed an ML-based CDS algorithm to identify the risk of a return to the ED for a fall for discharged patients [20]. This algorithm was subsequently incorporated into the EHR (Epic Systems). When providers are preparing to discharge a patient, this CDS alerts the ED provider if the ML algorithm identified the patient as at high risk of an at-home fall in the next 6 months and recommends referral to an outpatient mobility and falls clinic [21]. This process is illustrated in Figure 1 [21]. The ML algorithm will be retrained with the same feature set for each site prior to implementation. Implementation at each site will be done in compliance with institutional practice for CDS changes, following human factors engineering principles [23,24], and using best practices for ML-based CDS implementations [25].

**Figure 1 figure1:**
[figure not shown]
Operationalization of automated falls risk screening and referral process in the ED (adapted from Jacobsohn et al, reused with permission from Elsevier [21]). CDS: clinical decision support; ED: emergency department.

At the outpatient clinic, patients receive an evidence-based, multidisciplinary intervention to help them reduce their risk of a fall [13]. Together, the algorithm and associated CDS tool form a novel automated screening and referral intervention that was designed and implemented using a human factors engineering framework to ensure both usability and an emphasis on patient safety [21-23].

### Outcomes

Our primary outcome is the rate of completed referrals to the Mobility and Falls Clinic among patients identified as high-risk. We define a completed referral as a patient completing an initial visit with a falls prevention specialist at the mobility and falls clinic.

Our secondary outcome is return visits to any ED for a fall within 6 months of the index ED visit, the outcome our ML algorithm was trained to predict. This outcome is meant to reflect the overall effectiveness of the intervention in preventing falls among patients identified as high-risk.

Additional process outcomes will be investigated to deconstruct steps from the identification of high-risk patients to completed referrals. These include whether a patient was referred to the outpatient mobility and falls clinic after being identified as high risk, whether referred patients were reached by schedulers, and whether referred patients scheduled an initial appointment, regardless of whether they attended.

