### Statistical Analyses

#### Primary Outcome: Completed Referrals

The primary association of interest is whether an ED-based referral from an ML-based CDS can successfully cause patients to complete a specialist appointment. To assess the effectiveness of our program for patients receiving the falls risk intervention, our primary analysis will be to obtain point estimates and the 95% Wald CI of referral completion rate by site. We will perform a similar analysis to identify rates for prespecified process metrics, including referral orders placed among flagged patients and clinic appointments scheduled among at-risk patients. Further, we will perform a secondary analysis to identify subgroups at risk for lower odds of referral completion using a logistic regression model for each site to predict referral completion as a function of demography (sex, age, race, ethnicity, and education) and fall risk score. A model built for each site will account for site-level variability. Estimated coefficients and their 95% CIs will indicate risk factors for poor referral completion. This will help inform future implementation by, for example, identifying risk score thresholds for obtaining target rates of completed referrals for a given patient population.

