#### Statistical Power

With the plan to flag 5 patients per week at each referral site, we plan to refer 520 patients per site, generating 1560 total patients referred. A sample size of 520 would lead to 95% Wald CI for referral completion rate by site that is 8.6% in width or smaller. This width provides sufficient precision for our study, considering that (1) a completion rate as small as 10% would be clinically meaningful and (2) we expect to observe a referral completion rate of 50% or higher—in which case, there would be nearly 100% power to reject a referral completion rate of 10% at a significance level of .05 when n=520.

For reference, very few patients were referred from the ED to the mobility and falls clinic prior to our intervention, and the clinic estimates that 80% of their patients referred from other providers visit the clinic. Power can be estimated for detecting a significant intervention effect on fall risk, provided additional covariates are ignored. In this case, a score test for this effect is equivalent to a Cochran-Mantel-Haenszel test of independence in a stratified sample. Such a test has 89.7% power to detect a difference in fall risk of 10% in a stratified sample size of 12 groups (in twelve 8-week periods over 2 years) assuming (1) a significance level of .05, (2) 40 patients receive the intervention and 40 patients do not who have similar risk scores, and (3) an average fall risk of 25%. For reference, our preliminary work predicted a number to treat of about 10 (ie, a fall risk difference of 10%) when setting the risk score threshold so that 5 persons per week receive the intervention (or 40 persons per 8 weeks) and an average fall risk of about 25% for individuals with a fall risk score above or near the fall risk score threshold. We plan on exploratory analysis of pooled data to evaluate the effect of specific covariates on rates of referral; in these cases, power will be lower based on the incidence of specific covariates in the data.

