## Results

As of April 30, 2023, the CDS tool has been implemented at 2 of the 3 sites. Providers at ED 1 have written 303 referral orders for 260 unique patients, or 5 referrals per week on average, which is our goal. ED 2, the community ED, has not been live with the ML-CDS as long, and providers have written 91 referral orders for 86 different patients, or just over 3 referrals per week. Both EDs refer roughly 30% of patient encounters the algorithm identifies: 303 referrals for 1007 patients flagged at ED 1 and 91 referrals for 319 patients flagged at ED 2. The patient populations between these 2 EDs have substantial overlap, and 6 patients have received referrals from both EDs. After conversations with the mobility and falls clinic, we do not see repeat referrals as a problem unless the patient has already completed 1 of the referrals, so our ML-CDS tool was updated to exclude patients with a completed or scheduled appointment at the mobility and falls clinic. Notably, the patient uptake of the final intervention is about 15% of patients referred—45 patients of 339 unique patients; 1 patient was seen at and referred by both ED 1 and 2—which is less than the 80% that the clinic estimates for other referral sources. While not surprising that uptake would be lower from ED provider referrals than from primary care provider referrals, this conversion rate is lower than we anticipated, and we have taken steps to improve messaging, patient follow-up, and providers’ ability to talk to patients about the program, and we have taken other steps that have shown some improvement appointment conversion in recent months. Additionally, waning concerns about COVID-19 have seemed to increase patients’ willingness to consider completing the referral.

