### Significance of Principal Findings

Previous work with ML-CDS tools has focused on their implementation in a specific context [33] or on the predictive performance [34] of the underlying algorithm. Our unique data set will include information about patient’s health history (eg, health care use) prior to the ED index visit, referral completion, and subsequent ED return visits for falls (either in the system or from Medicare claims), providing a more complete picture of a given patient’s trajectory than most studies. We will use this unique data set to track not just ML-CDS performance in the context of its implementation, but in the context of larger patient health outcomes, which, to our knowledge, has not been done for this kind of long-term, preventative ML-CDS system. Similarly, the multisite implementation plan will demonstrate applicability to a broad population and the possibility to adapt the intervention to other EDs and achieve similar results.

Our statistical methodology (a regression discontinuity design) allows for an intent-to-treat causal inference about the impact flagging high-risk patients can have on patients’ future falls. Conversations with patients about the referral, even if a referral is not written, could have impacts on patients’ risk awareness and compliance with physical therapy, so ML-CDS flagging is the correct epidemiologic exposure to assess with respect to the outcomes of completed mobility and falls visits or return ED visits for falls. A staggered implementation strategy allows for the identification of secular trends that could affect causal association and mitigation as necessary.

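### The primary rate is defined among flagged patients but planned and tracked among referred patients, and only about 30% of flagged encounters led to a referral

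*Protocol article*

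**What the plan says.** The Outcomes section of the protocol article defines the primary outcome: "Our primary outcome is the rate of completed referrals to the Mobility and Falls Clinic among patients identified as high-risk". The numerator is a completed visit: "We define a completed referral as a patient completing an initial visit with a falls prevention specialist at the mobility and falls clinic". The same section lists, as a separate process outcome, "whether a patient was referred to the outpatient mobility and falls clinic after being identified as high risk". Flagging and referring are therefore two distinct steps in the plan. Significance of Principal Findings takes the same position: "ML-CDS flagging is the correct epidemiologic exposure to assess with respect to the outcomes of completed mobility and falls visits".

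The section on the primary analysis does not name the denominator: "our primary analysis will be to obtain point estimates and the 95% Wald CI of referral completion rate by site". It does name denominators for the process metrics that follow.

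The Statistical Power section begins: "With the plan to flag 5 patients per week at each referral site, we plan to refer 520 patients per site". For n=520 it gives a Wald interval at most 8.6% wide, treats a completion rate of 10% as clinically meaningful, expects 50% or higher, and claims nearly 100% power to reject 10%. Its reference figure is the clinic's estimate that 80% of patients referred by other providers attend.

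The Results section reports: "Both EDs refer roughly 30% of patient encounters the algorithm identifies". It tracks progress on the referred denominator: "the patient uptake of the final intervention is about 15% of patients referred", given as 45 of 339 unique patients.

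**The concern.** The planning text treats each flag as a referral. If every flag became a referral, the two denominators would coincide and nothing would be wrong. The article's own counts show that about 70% of flagged encounters do not lead to a referral, so a rate among flagged patients and a rate among referred patients differ by a factor of about three.

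Two things are at stake. First, the expected rate and the 80% reference do not describe the endpoint as defined, and the 10% benchmark means something different on each denominator. Second, the primary analysis names no denominator while interim counts are already published. Unless it is fixed, the denominator of the headline rate could be settled after the effect of the choice is visible.

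**Working it through.** **Inputs.** Statistical Power: 5 per week, n=520 per site, benchmark 10%, expected rate 50% or higher, reference 80%, significance level .05 (taken as two-sided). Results: 303 referral orders for 1007 flagged at ED 1; 91 for 319 at ED 2; 45 of 339 unique referred patients. Abstract: 1326 flagged encounters; the 45 are described as having scheduled an appointment.

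**1. Reproduce the plan's figures.**
- 5 × 104 weeks = 520; 520 × 3 sites = 1560.
- Widest Wald interval: 2 × 1.96 × √(0.5 × 0.5 / 520) = 8.6%.
- Power for 50% against 10% at n=520, normal approximation: 100% to rounding.

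The arithmetic is sound. The question is which 520 patients it describes.

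**2. From flag to referral.**
- ED 1: 303/1007 = 30.1%. ED 2: 91/319 = 28.5%. Together: 394/1326 = 29.7%.
- ED 1 was live for 61.7 weeks to April 30, 2023: 1007/61.7 = 16.3 flags per week and 303/61.7 = 4.9 referral orders per week. The planned 5 per week has been met as referrals, not as flags.

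**3. One numerator, two denominators.**
- Among referred: 45/339 = 13.3% (the article rounds to about 15%). Interval: 0.1327 ± 1.96 × √(0.1327 × 0.8673 / 339) = 9.7% to 16.9%.
- Among flagged encounters: 45/1326 = 3.4%. Interval: 0.0339 ± 1.96 × √(0.0339 × 0.9661 / 1326) = 2.4% to 4.4%.
- The number of unique flagged patients is not given. If flags repeat as referral orders did (394 orders for 339 patients), it is about 1326 × 339/394 = 1141, and the rate is 45/1141 = 3.9%. For 45 to reach 10%, unique flagged patients could number at most 45/0.10 = 450.

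**4. The planning figures on the flagged denominator**, at 30% referral:

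| Completion among referred | Rate among flagged |
|---|---|
| 50% (expected) | 0.30 × 0.50 = 15% |
| 80% (reference) | 0.30 × 0.80 = 24% |
| 100% (ceiling) | 30% |

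A rate of 10% among flagged needs 0.10/0.297 = 34% completion among referred.

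**5. Power for 15% against 10%, n=520 flagged.** (0.15 − 0.10 − 1.96 × √(0.10 × 0.90/520)) / √(0.15 × 0.85/520) = (0.0500 − 0.0258)/0.0157 = 1.55, so power is 93.9% (exact binomial 92.3%).

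**6. Numbers needed.**
- 520 flagged yield about 0.30 × 520 = 156 referred, for whom the widest Wald interval is 2 × 1.96 × √(0.25/156) = 15.7%.
- 520 referred need about 520 × 1326/394 = 1750 flagged per site.

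**The case against.** The best defence is that the outcome is already defined correctly and only the planning paragraph slips. The Outcomes section names flagged patients, and the Results section is a progress report whose referred denominator fits a listed process outcome. The 8.6% maximum width, which is the stated precision aim, holds for any 520 patients. All of this stands. It limits the point to an inconsistency that can be mended by rewording and restating figures; the design is not broken. It does not remove the point, because no section reconciles the 520 referred, the 50% expectation and the 80% reference with a flagged denominator.

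A reader might infer three stronger things that the document does not support.

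- *That the same data already give opposite conclusions on the primary endpoint.* The endpoint is a completed visit, whereas the Abstract describes the 45 as scheduled. The referred rate stays above 10% only if at least 34 of them attended (34/339 = 10.03%). The interval among referred patients includes 10%. The planned primary analysis is estimation, and 10% is a planning benchmark, not a decision rule.
- *That 50% among flagged patients is impossible.* The 30% ceiling is an interim, encounter-level observation, and it assumes that visits arise only through these referrals. The Limitations section describes efforts to raise referral and completion.
- *That the provider step drops out of the evaluation.* Referral orders among flagged patients are a prespecified process metric and would be reported under either denominator.

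**Conclusion.** The point holds as an inconsistency between the defined primary outcome and its planning figures. On the published counts the choice of denominator moves the rate from 13.3% to about 3.4%, or 3.9% after an assumed correction for repeat flags. The point estimates fall on either side of 10%, although the interval for the higher one includes 10%.

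At the observed referral rate, the stated expectation of 50% or higher cannot be reached on the defined denominator unless referral rises to at least 50%. The matching expectation is about 15%. At 520 flagged patients, power against 10% is then about 94%, not nearly 100%. That is still adequate, so the main fault lies in the expected rate, in what the benchmark means and in which patients n counts.

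These figures assume that referral stays near 30%, that completed visits come through these referrals, and that encounter-level rates approximate patient-level ones. The 45 are taken as the numerator although completed visits may be fewer; that would lower both rates.

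**What to change.** - In the section on the primary analysis and in Statistical Power, name unique patients flagged as high risk as the denominator of the primary rate, as the Outcomes section already does.
- Report completion among referred patients as a named process metric, and set the clinic's 80% beside that metric only.
- Restate the expected rate and power on the flagged denominator, and say whether the 10% benchmark is meant among flagged or among referred patients.
- State whether 520 per site counts flagged or referred patients, and give the conversion between them.

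The cost is rewording, a short recalculation, a lower headline rate and slightly less favourable stated power. The analysis also needs a count of unique flagged patients, which the article does not report.

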#### Secondary Outcome: Return Visits to ED for a Fall

Although the intervention is not randomized, our study has a quasi-experimental design known as a sharp regression discontinuity with regards to intent-to-treat, since the intervention is administered to patients whose risk score falls above some threshold. This design allows for causal inference, provided that differences in outcomes for patients with similar risk scores can be attributed to the intervention (formally, expected potential outcomes are continuous in risk score). This occurs when patients are not manipulating their assignment to the intervention. Assuming this holds, we will primarily analyze only those patients whose risk scores fall within a band around the risk score threshold. Additionally, patients will be stratified by ED arrival date to account for changes to this threshold to be aligned with a sharp research continuity design. A conditional logistic regression model will be built to describe 6-month fall risk at each site as a function of the intervention, patient demographics, and risk score. The odds ratio of a return visit for fall and the 95% CI will be estimated by comparing those identified as high risk by the ML-CDS algorithm and those who were not but had a similar risk profile. Sensitivity analyses will be performed to examine the influence of bandwidth choice and key assumptions (ie, continuity of potential outcomes and linearity in risk score) on estimates. A secondary analysis will be to investigate the effect of covariates on completed referrals and falls using a stratified Cox proportional hazards model for time-to-fall events (right-censored by follow-up time).

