### Limitations

To achieve the desired number of clinic referrals per week, the falls risk threshold for the CDS identification will be changed over time. Because regression discontinuity designs typically assume a static threshold for analysis, we will need to approach the regression discontinuity analysis carefully and with sufficient sensitivity analyses to ensure that these threshold changes do not compromise the findings. Simulation studies will be conducted to ensure the assumptions of regression discontinuity analysis are met.

Clinically, our assumptions about the effectiveness of the mobility and falls clinic intervention are based on PROFET (Prevention of Falls in the Elderly Trial) [13], which specifically evaluated patients referred from the ED. The intervention is based on evidence from a randomized clinical trial, but the magnitude of the effect may be different in our patient population—for example, due to endogenous factors like demographic composition of the community or exogenous factors related to changes in care patterns during the COVID-19 pandemic. In addition to methodological concerns, there are some pragmatic limitations. First, the intervention was implemented during the COVID-19 pandemic. During the study period and community, there were—and could continue to be—multiple waves of elevated SARS-CoV-2 infections and case counts that may dissuade some patients from scheduling an appointment at the mobility and falls clinic. Similarly, in order to maximize patient impact and to study the human factors inputs to this system, efforts were made to increase referral rates and referral completion with providers and patients. While these efforts will likely increase the statistical power over time, it is also likely that there will be secular effects in the imperfect compliance with referral rates and referral completion rates that are present in the data as a result of these efforts.

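### The falls result is presented as overall effectiveness in flagged patients, but the planned discontinuity analysis supports a conclusion only near the risk-score threshold(s) unless a constant effect is assumed

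*Protocol article*

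**What the plan says.** The Outcomes section defines the secondary outcome, return to any ED for a fall within 6 months, and gives its purpose: "This outcome is meant to reflect the overall effectiveness of the intervention in preventing falls among patients identified as high-risk". Significance of Principal Findings takes the same line, saying that the design permits "intent-to-treat causal inference about the impact flagging high-risk patients can have on patients’ future falls", with no restriction to patients near the cut-off.

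The method is in Secondary Outcome: Return Visits to ED for a Fall. It is a sharp regression discontinuity whose identifying condition is that "expected potential outcomes are continuous in risk score". On that basis, "we will primarily analyze only those patients whose risk scores fall within a band around the risk score threshold". Patients are stratified by arrival date because the threshold moves. A conditional logistic model will "describe 6-month fall risk at each site as a function of the intervention, patient demographics, and risk score", and the odds ratio comes from "comparing those identified as high risk by the ML-CDS algorithm and those who were not but had a similar risk profile". On robustness: "Sensitivity analyses will be performed to examine the influence of bandwidth choice and key assumptions", the named assumptions being continuity and linearity in the score.

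Limitations adds that "the falls risk threshold for the CDS identification will be changed over time". It also covers uncertainty about the size of the clinic's effect, COVID-19 and secular change. It does not say that the estimated effect is local to the threshold.

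**The concern.** A regression discontinuity answers a question about the margin: what being flagged does to someone whose score is close to the cut-off. Those are the flagged patients with the lowest scores. The article says the outcome speaks to effectiveness among the flagged group, which runs from the cut-off up to the highest scores. The two coincide only if the effect does not change with the score, or if nearly all flagged patients lie close to the cut-off.

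What is at stake is the reading of the result. A null finding near the cut-off could be taken to mean that the programme fails for high-risk patients in general, and a positive one to mean that every flagged patient benefits. Neither follows without a further assumption, and the article does not tell the reader that one is needed.

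**Working it through.** The plan attaches no figure to this point, so the main check sets the sections side by side.

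1. **Who the claim covers.** Outcomes and Significance of Principal Findings refer to flagged patients without restriction.
2. **Who the analysis covers.** The primary falls analysis uses patients in the band only. Continuity of potential outcomes justifies comparing the two sides at the cut-off. It says nothing about what flagged patients with much higher scores would have experienced unflagged.
3. **What would bridge the two.** A single odds ratio that is constant in the score would carry the result upwards. The model as described has terms for intervention, demographics and score. No intervention-by-score term and no constant-effect assumption is stated.
4. **Whether the sensitivity analyses test it.** They address bandwidth, continuity and linearity in the score. None is described as asking whether the effect of flagging varies with the score. The secondary Cox model investigates covariates and is not offered as an estimate of the overall effect.
5. **Whether the moving threshold closes the gap.** It widens coverage, because several cut-offs contribute. But the analysis is stratified by arrival date, so within each period flagged patients far above that period's cut-off still lack comparators.
6. **Whether a constant effect can be taken for granted.** The article gives reasons for doubt. Data Retrieval Process lists hospice, memory care and immobility among the reasons for ineligibility for the clinic. If such patients cluster at high scores (an assumption, not stated), benefit there could be smaller. Primary Outcome: Completed Referrals models completion on the risk score, so uptake is allowed to vary with it. A constant relative effect would instead give larger absolute benefit at higher risk. The direction is therefore open.

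**Illustration of size (assumed values).** Let *s* be the share of flagged patients in the band, 10 points the effect there (the planning difference in Statistical Power), and *x* the unidentified effect above the band.

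Average over all flagged patients = *s* × 10 + (1 − *s*) × *x*

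For *s*, the power calculation compares 40 intervention patients per 8 weeks, or 5 per week. Results gives flagged encounters to April 30, 2023:

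- ED 1, live since February 22, 2022: 432 days / 7 = 61.7 weeks; 1007 / 61.7 = 16.3 per week; 5 / 16.3 = 0.31
- ED 2, live since September 27, 2022: 215 days / 7 = 30.7 weeks; 319 / 30.7 = 10.4 per week; 5 / 10.4 = 0.48

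This assumes that the 5 per week are the flagged patients in the band and that flagging continues at the observed rate. The article gives no bandwidth, so *s* is not known.

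| *s* | *x* = 0 | *x* = 5 | *x* = 10 | *x* = 15 |
|---|---|---|---|---|
| 0.31 | 3.1 | 6.55 | 10.0 | 13.45 |
| 0.48 | 4.8 | 7.4 | 10.0 | 12.6 |

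The band effect equals the overall average only when *x* = 10 or *s* = 1. The table uses risk differences because the planning value is one; the planned estimate is an odds ratio. It shows that the band result leaves the overall figure open, and does not predict what that figure will be.

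**The case against.** The strongest reply is that the word overall means end-to-end. In Outcomes it contrasts falls with the intermediate steps of referral and scheduling, and the sentence describes an outcome without defining an estimand. The article also discloses the band and the similar-risk comparison, so a reader can see who is compared. That reading of the word is plausible. It still leaves the sentence's population, the flagged patients, broader than the analysis, and the article nowhere says that the effect is local. Nor is this a detail for an analysis plan that is not shown, because the article itself states a target and a method that do not match.

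Three stronger readings are tempting, and the documents do not support them.

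- **That the analysis speaks only to a single score, or cannot support the claim at all.** The odds ratio is fitted across a band, the word primarily leaves room for wider analyses, thresholds change, and the algorithm is retrained by site. With a stated and defended constant-effect assumption, the wider claim could be made.
- **That the cited 38% reduction shows the overall effect to be larger by a definite factor.** The risk at the threshold is not given, and uptake is far from full: about 30% of flagged encounters are referred, and about 15% of referred patients take it up. The planned measure is also an odds ratio. At assumed risks of 15% and 25%, a 38% reduction gives (0.093/0.907)/(0.15/0.85) = 0.58 and (0.155/0.845)/(0.25/0.75) = 0.55, which are nearly equal.
- **That the planned number to treat of about 10 refers to a different population from the result.** In Statistical Power, the wording about patients above or near the threshold qualifies the 25% average risk, not the number to treat.

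It also stands that the power calculation treats every planned intervention patient as part of the comparison, so the planners may not have seen the band as a thin slice. Observed flagging runs at two to three times the planned 5 per week, so that equivalence cannot be presumed.

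**Conclusion.** The point holds as wording that claims more than the analysis identifies. The falls analysis estimates the effect of being flagged for patients near the threshold(s) in force at each site, averaged over threshold periods, and over sites if the site results are combined. It does not by itself support a conclusion about all flagged patients. That would need an assumption that the odds ratio is constant in the risk score, which is neither stated nor examined.

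The conclusion rests on the article's own text and on the standard identification argument for a discontinuity design, not on the illustrative figures. The documents settle neither the size nor the direction of any difference between marginal and overall effects. Nothing here questions the validity of the discontinuity estimate for patients near the threshold.

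**What to change.** 1. In Outcomes, say that the falls analysis estimates the effect of being flagged on 6-month ED return for a fall among patients near the risk threshold(s). Restrict the causal statement in Significance of Principal Findings in the same way.
2. In Limitations, add that the effect is local to the threshold(s) and that flagged patients well above them have no comparable unflagged patients.
3. Label any statement about all flagged patients as an extrapolation, and state the constant-odds-ratio assumption it needs. Examine that assumption, for example by comparing effects across threshold periods. This is a partial check, since the article itself expects secular changes in referral and completion over the same periods.

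Reporting the share of flagged patients inside the band and the risk near the threshold would help readers judge the extrapolation, but this is secondary reporting detail. No new data, change of design or change to the main model is needed. The only cost is a narrower claim.
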